| 4. The purpose of the study and its objectives; indication of the hypotheses, separated into primary and secondary hypotheses as well as the clinical parameters (primary and secondary endpoints), on the basis of which the hypotheses checked                                                                                                                                                                                                                                                                                     | The purpose of the study is the analysis and prediction of the hemodynamic result of interventions in patients with heart disease, particularly stenosis of the aortic isthmus, the pulmonary arteries and the aortic valve. To this end, image-based (MRI) modeling of the function
Hypothesis: The image-based modeling can predict hemodynamic parameters. Thus, for a diagnostic heart catheter examination could be replaced, and the hemodynamic effects before the intervention can be simulated and optimized, aiming towards optimized outcome.                                                                                                                                                                                                          |

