| 9. Substantial content and results of the previous studies/applications of research in the study of products to be tested                                                                                               | n.a.                                                                                                                                                                                                                                                                                                                                                                                                                                                                                    |
| 10. Description of the planned measures/methods of investigation and any deviations from the practice in the med. Usual measures/Studies (what is "routine", what is different in the study done?)                      | MR image data as well as the pressure values of heart catheter investigations are carried out in the framework of routine diagnostics will be used for the image-based modeling.
In patients consenting an MRI exam after an intervention (heart catheter or surgery) will be scheduled without the use of contrast agent. If after intervention (heart catheter or surgery) a clinical indication for an MRI control exists, any of these data is also be supplied to the analysis. |
| 11. Evaluation and consideration of the foreseeable risks and disadvantages of study participation against the expected benefits for the study participants and will in future be ill persons (benefit-risk assessment) | Disadvantages are not to be expected.                                                                                                                                                                                                                                                                                                                                                                                                                                                   |

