| 15. Biometric planning with specification of the statistical methodology, including the justification for the case number. Indication of the statistician/Statistics Erin                                               | n.a., because it is a pilot study.                                                                                                                                                                                                                                                                                                                                                                                                                                                      |

|                                                                                                                                                                                                                                                                       |                                                                                                                                                                                                                                                                  |
|-----------------------------------------------------------------------------------------------------------------------------------------------------------------------------------------------------------------------------------------------------------------------|------------------------------------------------------------------------------------------------------------------------------------------------------------------------------------------------------------------------------------------------------------------|
| 16.
A. Presentation and any explanation of the inclusion and exclusion criteria                                                                                                                                                                             | Inclusion criteria were any of the following diseases: pulmonary stenosis, aortic coarctation, aortic aortic valve disease in which MRI image data are available with the intervention                                                                           |

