| Participant information (presented orally and in writing and specify how much time remains between information and Consent (written information as an attachment)                                                                                              | Orally by the leader of the study or study physicians as well as written participant information and informed consent (see appendix)                                                                                                                             |
| C). A Declaration of Consent (written form as attachment)                                                                                                                                                                                                      | See Appendix                                                                                                                                                                                                                                                     |
| D. If necessary information and consent of the legal representative (if necessary, also the description of the procedure for the establishment of a judicial support)                                                                                          | See 16.c                                                                                                                                                                                                                                                         |
| 17. Measures for the recovery of study participants (Notifications, announcements etc).                                                                                                                                                                               | Recruitment from the current or future patient collective                                                                                                                                                                                                        |

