| 18. If necessary: the reason for the inclusion and explanation of the therapeutic benefits for persons under age of 18 and/or the need for consent by a legal representative.                                                                                  | In congenital heart disease stenoses of the vessels (e.g., coarctation), and aortic valve disease (bicuspid aortic valve disease) are frequent congenital heart diseases, and often require interventions in children and in the course of growth are necessary. |
| 19. Relationship between study participants and study doctor/doctor (is the study doctor at the same time the doctor?)                                                                                                                                                | The study physician is also the treating physician.                                                                                                                                                                                                              |
| 20. Declaration on the inclusion of possible from the Sponsor dependent persons                                                                                                                                                                                       | n.a.                                                                                                                                                                                                                                                             |
| 21. Measures which allow a determination as to whether a study participants can be participating in several studies at the same time or before the expiry of a specified in the previous study period takes part
is the participation in several studies possible? | A simultaneous participation in another study is possible.                                                                                                                                                                                                       |

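### Eligibility by available MRI data, open to current patients and with no rule to take every eligible case, permits selection with scan and catheter result known and may overstate model accuracy

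*Protocol*

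**What the plan says.** All references are to the protocol.

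- **Item 16.A (inclusion and exclusion criteria):** pulmonary stenosis, aortic coarctation or aortic valve disease, "in which MRI image data are available with the intervention". The item gives no exclusion criterion, image-quality rule or consecutive-enrolment rule.
- **Item 17 (recruitment):** "Recruitment from the current or future patient collective".
- **Item 10 (methods):** the inputs are routine data: "MR image data as well as the pressure values of heart catheter investigations are carried out in the framework of routine diagnostics". One part is prospective: "In patients consenting an MRI exam after an intervention (heart catheter or surgery) will be scheduled".
- **Item 14 (numbers):** 20, 40 and 60 patients in the three disease groups, without a rule on which eligible patients fill them.
- **Item 16 (participant information) and item 19:** information is given "Orally by the leader of the study or study physicians", and "The study physician is also the treating physician".
- **Item 4 (hypothesis):** "The image-based modeling can predict hemodynamic parameters", with the prospect that "for a diagnostic heart catheter examination could be replaced".

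**The concern.** A study of how well a model predicts a measured reference value depends on how its cases come in. If the person deciding whom to approach can already see the scan and the catheter pressure, difficult cases can be passed over, knowingly or not. Patients whose MRI was not done or failed may leave no trace at all.

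Two results are at stake. One is the agreement between model and catheter, which may look better than it would in all eligible patients. The other is feasibility, meaning how often the MRI route yields an answer; the idea of replacing a diagnostic catheter depends on this just as much.

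This is a protocol matter. Items 16.A and 17 are where the form asks for eligibility and recruitment, and no later analysis plan can recover patients who were never registered.

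**Working it through.** **No figure to reproduce.** Item 15 declares biometric planning not applicable because this is a pilot, and the protocol states no accuracy, SD or margin. The check is therefore a reading of the items together, followed by illustrations on stated assumptions.

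**Step 1: what can be known at inclusion.** Item 10 makes both MRI and catheter pressure routine data. Item 17 lets current patients in. For them, both may be on file when they are approached. For future patients this need not be so. Item 14 sets group sizes of 20 + 40 + 60 = 120, and no item says that all eligible patients, or consecutive ones, fill them.

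**Step 2: effect on agreement.** Set the SD of the prediction error in all eligible patients to 1.00 (normal errors, 1,000,000 draws). Let selection follow a score with correlation rho to the rank-normalised closeness of prediction. Rho and the share left out are assumptions. SD among those included:

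| rho | 10% left out | 20% | 30% | 50% |
|---|---|---|---|---|
| −0.4 (harder cases favoured) | 1.03 | 1.07 | 1.10 | 1.17 |
| 0 (unrelated to error) | 1.00 | 1.00 | 1.00 | 1.00 |
| 0.2 | 0.97 | 0.95 | 0.94 | 0.90 |
| 0.4 | 0.94 | 0.90 | 0.86 | 0.79 |
| 0.6 | 0.90 | 0.83 | 0.78 | 0.67 |

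**Step 3: upper bound for a given share left out.** If exactly the most discordant fraction t were dropped, the SD would be sqrt(1 − 2c·φ(c)/(1 − t)), with c = z(1 − t/2). For t = 0.05, 0.10 and 0.20 this gives 0.871, 0.789 and 0.662, so limits of agreement 13%, 21% and 34% too narrow. This assumes perfect selection on model error, a quantity that exists only once the model has been run. It is a ceiling, not an estimate.

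**Step 4: effect on feasibility, illustration only.** Assume modelling succeeds in 90% of patients with usable MRI, and that a fraction f of eligible patients has none and never enters. Success among all is 0.90 × (1 − f): for f = 0.1, 0.2 and 0.3 it is 81%, 72% and 63%. This needs no correlation with error, but both inputs are assumed.

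**Step 5: could the collected data show the problem?** The 95% half-width for a limit of agreement is about 1.96·sqrt(1/n + 1.96²/(2(n − 1))) in SD units: 0.76, 0.53 and 0.44 for n = 20, 40 and 60. At rho = 0.4 with 20% left out, each limit shifts by 1.96 × (1 − 0.899) = 0.20 SD. That is smaller than the sampling uncertainty even in the largest group, and without a log there are no omitted patients to compare with.

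**The case against.** The case against is substantial.

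- **The criterion is inherent to the method.** An MRI-based model needs MRI. Item 16.A sets no quality threshold, so a poor scan still qualifies, and its wording can be read as imaging around the time of treatment. This stands: requiring MRI is not a fault. What remains is the missing rule on taking all who meet it.
- **A reader might infer that accuracy will be overstated.** The protocol does not support that. Selection unrelated to model error leaves the SD unchanged, and favouring harder cases understates accuracy.
- **A reader might infer that treating physicians pick the cases.** Item 19 answers an ethics-form question about the doctor–patient relationship, and item 16 says who informs participants. Neither describes case selection. The double role makes knowledge of results plausible and shows no more than that.
- **A reader might take 13% to 34% as the expected bias.** Nothing places the modelling before inclusion. Knowing a scan and a pressure is not knowing how far the model will miss.
- **The study is a pilot, and replacing the catheter is a hope rather than a claim.** True, and this limits how serious the point is. But selection also affects a pilot, and later studies would be planned on its figures.
- **Future patients are eligible and the post-treatment MRI is prospective.** This also stands, and it narrows the problem to cases whose results were known at inclusion and to eligible patients not approached.

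**Conclusion.** The point holds as a cheap improvement. The entry and recruitment rules together allow current patients to be included with scan and reference value already known, and no rule requires that all eligible patients be approached. Accuracy and feasibility may therefore be overstated.

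Direction and size cannot be derived from the protocol. With 10% to 50% left out, moderate selection on closeness of prediction (rho 0.2 to 0.6) would lower the apparent error SD by between 3% and 33%, while no or opposite selection would leave it unchanged or raise it by up to 17% (rho = −0.4). These ranges rest on normal errors and on assumed values of rho and of the share left out. The conclusion that the plan permits such selection needs none of those assumptions; it follows from items 10, 16.A and 17 read together.

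**What to change.** In items 16.A and 17:

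1. Within each of the three disease groups, approach consecutive eligible patients undergoing treatment.
2. Keep a screening log with reasons for non-inclusion, including MRI not done or unusable, and report these counts beside the accuracy result.
3. Keep included patients whose scan cannot be modelled in the feasibility denominator.
4. Record on the eCRF whether the catheter result was known at inclusion, and report those patients separately. Where the group is small, as with the 20 patients with pulmonary stenosis, a sensitivity analysis is enough.

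Registering every patient when the MRI is requested would be a larger design change and is not needed.

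**Cost:** wording in two items, a log and one eCRF field. The figures may turn out less favourable, and the subset with unknown results is less precise. If, say, half of the 20 had known results, the half-width for a limit of agreement in the other 10 would be 1.96 × sqrt(1/10 + 1.96²/18) = 1.10 SD, against 0.76 SD for all 20. That is why a sensitivity analysis suits this group better than a separate main estimate.

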|---------------------------------------------------------------------------------------------------------------------------------------------------------------------------------------------------------------------------------------------------------------------------------------------------------------------------------------------------------------------------|----------------------------------------------------------------------------------------------------------------------------------------------------------------------------------------------------------------------------------------------|
| Possibility.                                                                                                                                                                                                                                                                                                                                                              | Study physicians: Dr . [name]
[name]                                                                                                                                                                                           |
| 31. Information on the suitability of the inspection body, in particular regarding the appropriateness of the existing resources and facilities as well as the conduct of the clinical trial available personnel and experience in the implementation of similar studies                                                                                                  | At the DHZB and the Charité many patients with congenital and acquired heart disease are being examined using MRI, as well as in the heart catheter lab. For MRI imaging state-of-the-art equipment is available.                            |
| 32. Agreement on access of auditor/principal auditor/head of the clinical examination, to the data and the principles concerning the publication .
- publications in a form that no conclusion on the individual.
- if necessary the access to specific data for the
Legally justified auditor (third parties) to
Dedicated access to the
Necessary files. | The study leader and commissioned staff have access to in the framework of the study collected data. Decisions regarding the publication of the data are the responsibility of the director of studies. The publication is always anonymous. |
